## Background

Sleep disorders are common throughout the world and have living effects on modern industrialized "24-hour" societies. The consequences of such disorders include excessive sleepiness, a negative effect on social and recreational activities, a decreased physical ability, a decline in productivity and a high risk of accidents [1]. These conditions, which are associated to acute or chronic insomnia, chronic sleep restriction, work shifts, jet lag, narcolepsy and obstructive sleep apnea (OSA), are a public health concern.

There is a large body of evidence demonstrating that sleepiness contributes toward industrial and traffic accidents [2]. It has previous been reported that 22% of accidents are caused by excessive sleepiness and 17-19% of traffic deaths are the result of sleepiness at the wheel [3]. The medical and economic costs of traffic accidents are estimated to be 1 to 3% of the gross domestic product of a country (annual cost of approximately 518 billion dollars). The *Instituto de Pesquisa Econômica Aplicada *(IPEA) [Institute of Applied Economic Research] of the Brazilian Federal Government reports that the mean cost of traffic accidents in Brazil is US$ 5,167,000, among which US$ 1,919.000 are spent on victimless accidents, US$ 2,942,000 are spent on accidents that result in injuries and US$ 2,476,000 are spent on accidents involving deaths [4].

OSA is a respiratory disease characterized by the collapse of the upper airways which occurs during sleep in predisposed subjects. Following chronic obstructive pulmonary disease and asthma, OSA is the epidemiological most important and widespread respiratory disease, affecting 3 to 7% of the male population and 2 to 5% of the female population between 40 and 65 years of age in the western world [5]. In Brazil, prevalence even larger was encountered according to an epidemiological study carried out in the city of Sao Paulo, where 24.8% males and 9.6% females were OSA patients [6].

One of the most important social implications of OSA is the increased risk for driving accidents [7]. Pack et al. (2002) reported a prevalence of 28% in a population of professional truck drivers [8]. The main cause of road accidents among professional drivers is lack of sleep, disturbance in the sleep/wake cycle (shift workers) and sleep disorders [9,10].

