**Figure 2 F2:**
[figure not shown]
**Schematic representation of the negative expiratory pressure apparatus**.

NEP maneuvers will be performed (each after at least four breaths to normalize the breathing pattern). The tests will be carried out once with the subjects seated comfortably and one other in supine position on a cot. In both positions, care will be taken to maintain the subjects comfortable with the neck in a neutral position, as it has been documented that the position of the head exerts an influence over upper airway collapsibility [40]. All maneuvers will be performed with the subjects awake and wearing a nose clip. The airflow and the mouth pressure signals will be low-pass filtered and sampled at 200 Hz. Both digital signals will be displayed in real time on the monitor and stored on the computer for subsequent analysis. Signal analysis and solenoid valve control will be performed using software written in Labview 8.2 (National Instruments) developed by the Italian National Research Council, Institute of Biomedicine and Molecular Immunology "A. Monroy".

NEP application during tidal expiration produces an immediate peak flow followed by a sudden drop of a variable degree. Upper airway collapsibility is evaluated by measuring flow limitation as flow drop (Δ$\dot{\text{V}}$), expressed as the percentage of peak flow immediately after NEP administration. To avoid reflex and voluntary reactions to the NEP stimulus, the minimal flow will be identified in the first 200 ms of NEP administration [41]. Upper airway collapsibility is also evaluated by measuring V_0.2 _immediately after NEP administration (Figure 3). These values are expressed as the percentage of mean inspiratory volume of the three breaths preceding NEP administration. Measured volumes are accepted only when differences between inspiration and expiration for each of the three previous breaths are less than 10%. Values of V_0.2 _and Δ$\dot{\text{V}}$ (%) are calculated as the mean of four measurements.

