### Standard overnight polysomnography

Nocturnal polysomnography will be carried out using the Embla Somnologica Studio - EMBLA A10, version 3.1.2. (Flaga hf. Medical Devices, Iceland) sleep analysis system. The following signals will be recorded: electroencephalogram (F4-M1, C4-M1, O2-M1, and backup electrodes F3, C3, O1 and M2), electrooculograms (E1-M2, E2-M2), chin and tibials electromyography, electrocardiogram, oxygen saturation, pulse rate, oronasal airflow (nasal canula and thermistor), respiratory effort (thoracic and abdominal Xtrace model straps), snoring, and body position. The patients will be instructed to remain relaxed and sleep naturally as at home. Throughout the night, the subjects will be monitored by a technician experienced in polysomnography [42]. The reading will be performed by professionals who were blinded to the result of the NEP test, following the guidelines of the American Academy of Sleep Medicine [43] and criteria of the Brazilian Sleep Society.

Apneas are defined as lack of airflow or a reduction ≥90% in the airflow signal for at least 10 s. Hypopneas are defined as discernible drop in flow by ≥ 30% of baseline for a period lasting at least 10 s followed by a SaO_2 _fall ≥4%. AHI will be calculated as number of (apneas + hypopneas)/h of total sleep time. Subjects with AHI ≥5 will be classified as OSA [42,43].

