### Calculation of sample size and statistical analysis

The calculation of sample size was based on the correlation reported by Insalaco et al. [44] between Δ$\dot{\text{V}}$(%) and AHI in patients with OSA (r = 0.37). For a bidirectional alpha value of 0.05 and 90% power, a minimum number of 82 subjects will be necessary.

Kolmogorov-Smirnov normality test will first be performed in order to determine the presence or absence of a normal distribution sample. Descriptive analysis will be performed, with the data expressed as either mean and standard deviation or median values and 95% confidence intervals, when appropriate. One-way analysis of variance (ANOVA) will be used for comparisons between work shifts once the samples have a normal distribution. V_0.2 _and Δ$\dot{\text{V}}$(%) values will be linearly correlated with the AHI, for which either Pearson's or Spearman's correlation test will be used, depending on the sample distribution. Either the non-paired Student's t-test or Mann-Whitney test will be used for comparisons between individuals with and without OSA. Logistic regression for the analysis of continuous factors with categorical responses will be performed. Receiver operating characteristic (ROC) curves will be constructed to determine the sensitivity (true positive rate) versus 100-specificity (false positive rate) at various levels of the measured Δ$\dot{\text{V}}$ (%) and V_0.2 _(%) to identify the cut-off value yielding the largest number of correctly classified patients. The statistical analysis will be performed by an experienced statistician using the JMP commercial program (version 8.0, SAS Institute Inc.) and SPSS program (version 16.0, Somers NY). A 5% level of significance and 95% confidence interval will be applied.

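### Naming Welch's t-test instead of Student's would protect the OSA versus no-OSA comparison if the groups are unequal in both size and spread (minor)

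*Protocol article*

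**What the plan says.** The analysis section of the protocol article (Calculation of sample size and statistical analysis) sets the two-group comparison: "Either the non-paired Student's t-test or Mann-Whitney test will be used for comparisons between individuals with and without OSA". The step before it is distributional: "Kolmogorov-Smirnov normality test will first be performed in order to determine the presence or absence of a normal distribution sample". No check of equal variances and no unequal-variance version of the t-test is mentioned. The general rule for inference is "A 5% level of significance and 95% confidence interval will be applied".

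The groups are defined under Standard overnight polysomnography: "Subjects with AHI ≥5 will be classified as OSA". Their sizes are therefore observed, not fixed by design. The article states no expected split. Background cites a Sao Paulo survey in which "24.8% males and 9.6% females were OSA patients", and a prevalence of 28% in professional truck drivers. The prevalence among these bus drivers is itself a secondary objective. The sample size statement is "For a bidirectional alpha value of 0.05 and 90% power, a minimum number of 82 subjects will be necessary", and it refers to the correlation of flow drop with AHI.

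**The concern.** The unpaired Student's test estimates one common variance. With equal group sizes, unequal spreads do little harm. With unequal sizes, the larger group dominates the pooled variance, and the standard error is wrong whenever the smaller group's spread is different. If the smaller group is the more variable, the test rejects too often and the interval is too narrow. If it is the less variable, the test is conservative, the interval is too wide and power is lost. A normality test does not detect either situation.

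Here the groups arise from a diagnostic threshold in an invited workforce, so a balanced split would be a coincidence. The main objective asks whether collapse induced by negative expiratory pressure (NEP) indicates the presence and severity of OSA. This comparison is one of the planned looks at presence. What is at stake is the accuracy of its p-value and 95% interval.

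**Working it through.** **The plan's own figure.** The only computed figure is the minimum of 82. With r = 0.37, two-sided alpha 0.05 and 90% power, Fisher's z gives n = ((1.960 + 1.282)/atanh(0.37))² + 3 = (3.242/0.3884)² + 3 = 72.6, so 73. The stated 82 is not reproduced but errs on the safe side (93.2% power at r = 0.37). It is a separate matter, and 82 is used below only as the total to be split.

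**Likely split (inferred).** 82 × 0.248 = 20.3, so 20:62. 82 × 0.28 = 23.0, so 23:59. Prevalences of 40% (33:49) and 50% (41:41) were added because the study's own prevalence is unknown.

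**SD ratio (assumption).** The article gives no SD for flow drop or V0.2 in either group. The ratio k = SD(OSA)/SD(non-OSA) was therefore run from 0.5 to 2.

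**Large-sample formula.** Let w be the OSA fraction. Up to a common factor:
- true variance of the mean difference: Vt = k²/w + 1/(1 − w)
- variance that the pooled test targets: Vs = (w·k² + 1 − w)·(1/w + 1/(1 − w))
- actual type I error = 2Φ(−1.96·√(Vs/Vt))

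Example with w = 0.248 and k = 1.5: Vt = 2.25/0.248 + 1/0.752 = 10.40. Vs = 1.310 × 5.362 = 7.02. √(7.02/10.40) = 0.82. The type I error is 2Φ(−1.61) = 10.7%. At k = 0.5, 0.67 and 2 the formula gives 0.7%, 1.7% and 15.1%.

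**Simulation** (normal data, equal means, nominal two-sided 5%, 100,000 runs per cell, N = 82). Type I error of Student's test:

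| Split | k = 0.5 | 0.67 | 0.8 | 1 | 1.25 | 1.5 | 2 |
|---|---|---|---|---|---|---|---|
| 20:62 | 0.8% | 1.7% | 2.8% | 5.0% | 8.0% | 10.7% | 15.6% |
| 23:59 | 1.1% | 2.1% | 3.1% | 5.0% | 7.5% | 9.8% | 13.8% |
| 33:49 | 2.9% | 3.5% | 4.2% | 5.1% | 6.1% | 6.8% | 8.3% |
| 41:41 | 5.1% | 5.0% | 5.1% | 5.0% | 5.0% | 5.1% | 5.0% |

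Welch's test gives 4.9% to 5.1% in every cell.

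**Interval coverage.** For given SDs, the coverage of the pooled 95% interval is 100% minus the tabulated error, whatever the true mean difference. At 20:62 that is 92.0% at k = 1.25, 89.3% at k = 1.5 and 98.3% at k = 0.67.

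**Larger samples.** The problem depends on the split, not on N. At N = 300 with 24.8% prevalence (74:226), Student's error runs from 0.7% to 15.4% for k from 0.5 to 2. With all 710 drivers at 28% (199:511), it runs from 1.1% to 13.6%.

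**Cost of Welch when the SDs are equal** (N = 82, Student against Welch). At a difference of 0.7 SD, power is 80.2% against 79.3% (23:59) and 76.7% against 75.2% (20:62). At 0.8 SD, it is 89.5% against 88.8% and 86.7% against 85.4%. The loss is 0.7 to 1.6 points.

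**The case against.** The strongest reply is that the decisive inputs are not in the document. No SD is given, so even the direction of any error is unknown. The split is borrowed from other populations, and the distortion falls away as prevalence approaches 50%. For SD ratios of 0.8 to 1.25 the error at 20:62 is only about 3% to 8%. All of this stands, and it is why the size is given as a range and the split as likely.

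Two stronger readings are tempting, but the document does not support them. The first is that the test must be wrong because groups will split 1:3 and spreads will differ. Neither is stated, and with equal groups a difference in spread is harmless. The second starts from flow drop being "expressed as the percentage of peak flow immediately after NEP administration". A reader might infer that the spread of a percentage moves with its mean, take a ratio such as √(0.4 × 0.6/(0.2 × 0.8)) = 1.22 for means of 20% and 40%, and quote an inflated false-positive rate. This does not follow. If the spread differs only because the means differ, equal means imply equal spreads and the error rate is 5%. Such a ratio bears only on interval coverage when a difference exists. The two means are also assumed: by the same formula, 40% and 60% give a ratio of 1.0, and 60% and 80% give 0.82.

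It can also be said that little rests on this test, and that an article may leave the variance version to the full protocol or statistical analysis plan. The first part stands: the sample size rests on the correlation and the cut-off on the ROC curves, and Mann-Whitney is the alternative for non-normal data. The second stands only in part. The article does not leave the test open; it names Student's, which is the pooled version.

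**Conclusion.** The point holds as a cheap improvement of minor priority, not as an error that undermines the plan. The article names a pooled-variance test, with a normality check only, for groups whose sizes are not under its control. If OSA prevalence is near the cited 24.8% to 28% and the spreads differ, the p-value and 95% interval can be materially off in either direction: about 3% to 8% type I error at 20:62 for SD ratios of 0.8 to 1.25, and 0.8% to about 16% for ratios of 0.5 to 2. At 40% prevalence the wider range narrows to 2.9% to 8.3%; near 50% nothing is lost. These figures assume normal data and a range of SD ratios that the document neither supplies nor excludes. They concern the t-test option only.

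**What to change.** In the sentence on comparing individuals with and without OSA, replace the unpaired Student's test with *Welch's unequal-variance t-test, with its 95% confidence interval for the mean difference*. Apply it without a preliminary variance test.

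Optionally, where the rank comparison is used, report beside it the area under the ROC curve with a 95% confidence interval, since ROC curves are already planned for both NEP measures.

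The cost is one sentence and about 1 to 2 power points if the SDs turn out to be equal. No change to the sample size, data collection or ROC cut-off is needed.

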There is a close relationship between OSA and the risk of cardiovascular disease [11-13], neuropsychological problems [14,15], reduction in quality of life [16,17] and increase in the use of health resources [18,19], demonstrating that, when under-diagnosed, OSA can have serious consequences. Thus, the identification of new markers for OSA can be of considerable relevance for clinical practice.

An increase in the upper airway collapsibility is one of the main determinants of OSA [20,21]. Investigators have identified anatomical factors [22-24], neuromuscular control factors [25,26] and liquid and fat deposits [27] that may lead to increased pharyngeal collapsibility during sleep.

The negative expiratory pressure (NEP) method was initially used to assess intrathoracic expiratory flow limitations in patients with chronic obstructive pulmonary disease [28]. However, NEP test in individuals with OSA was found to lead to a collapse of the extrathoracic airway, with a drop in expiratory flow below the preceding expiration, which is common among patients with OSA [29-32]. The NEP test is carried out by administering negative pressure at the mouth during expiration. This maneuver is easy to perform and requires minimal patient cooperation. NEP test is based on the pressure gradient increase between the alveoli and open upper airway that results in an increase in expiratory flow. This study will allow the use of new screening technique to detect upper airway collapsibility, a high risk indicator for OSA in professional drivers. It's a daytime, low-cost screening method that could be included in a preventive strategy aimed at reducing the impact of this condition on accidents and the development of cardiovascular consequences.

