## Discussion

Despite the abundance of scientific evidence, OSA is still underdiagnosed in the general population. This is probably due to multiple causes, such as deficiency of knowledge on the part of physicians and also the limited access of the patients to diagnosis and treatment of OSA [45]. In addition, diagnostic procedures are expensive, and predictive criteria are still unsatisfactory. Obesity parameters are important predictors, although not all OSA patients are obese and not all obese subjects have OSA. The identification of new markers of OSA would be useful.

The aim of the present protocol study is to determine whether the NEP test could be used as a screening tool for OSA and the prevalence of this condition among a population of professional interstate bus drivers. Because increased upper airway collapsibility is one of

the main determinants of OSA [21], the response to the application of NEP could be a predictor of this disorder.

With the enrollment of this study protocol, the expectation is to encounter predictive NEP values for different degrees of OSA. It's a daytime, low-cost screening method that could be included in a preventive strategy in order to contribute toward an early diagnosis of this condition and reduce its impact and complications among professional interstate bus drivers.

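### The rule for choosing the NEP cut-off depends on the OSA share of the sample and, at the prevalences cited, gives up sensitivity, which fits poorly with a screening aim

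*Protocol article*

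**What the plan says.** The section on sample size and statistical analysis plans ROC curves for the two NEP measures, flow drop (%) and V0.2 (%), and names a single purpose for them: "to identify the cut-off value yielding the largest number of correctly classified patients". The article gives no minimum sensitivity, no weighting of missed cases against false alarms and no alternative criterion.

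The intended use is screening. The Discussion gives the aim as "to determine whether the NEP test could be used as a screening tool for OSA", and the Background says of the test: "It's a daytime, low-cost screening method that could be included in a preventive strategy aimed at reducing the impact of this condition".

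The reference standard is polysomnography: "Subjects with AHI ≥5 will be classified as OSA". For prevalence, the Background cites a study that "reported a prevalence of 28% in a population of professional truck drivers", a Sao Paulo survey in which "24.8% males and 9.6% females were OSA patients", and a western figure, "affecting 3 to 7% of the male population". The only effect size is the correlation used for the sample size, between flow drop (%) "and AHI in patients with OSA (r = 0.37").

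**The concern.** The number correctly classified is N × [p × sensitivity + (1 − p) × specificity]. Two things follow.

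- The chosen cut-off is not a feature of the NEP test alone. It depends on p among those who volunteer, and volunteers need not mirror the 710 drivers invited.
- When p is below one half, as in every prevalence cited, the rule trades sensitivity for specificity. For a marker of moderate strength the trade can be severe.

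A published threshold is what later users of a screening test would adopt. A threshold chosen this way could pass over many drivers with OSA, or make a useful marker look weak. Either would undercut the Discussion's expectation of finding NEP values that predict OSA.

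**Working it through.** The protocol gives no AUC, sensitivity or specificity, so it has no figure of its own to reproduce on this point. Its sample size of 82 was set for the correlation and does not enter the check.

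**Inputs from the protocol.** p = 0.28 (truck drivers) and 0.248 (Sao Paulo males); r = 0.37, in OSA patients only.

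**Assumptions.** The NEP measure X, oriented so that higher means more collapsible, and a transformed AHI Y are bivariate normal with correlation ρ. OSA is Y > a, with a = Φ⁻¹(1 − p).

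**Step 1: relative weight.** One point of sensitivity against one of specificity is p/(1 − p): 0.248/0.752 = 0.33 and 0.28/0.72 = 0.39.

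**Step 2: two values for ρ.**
- Take r = 0.37 as the all-driver value. The AUC is then about 0.68.
- Correct for restriction to OSA patients. With λ = φ(a)/p, the variance of Y among cases is u = 1 − λ(λ − a), and ρ²/(1 − ρ²) = [r²/(1 − r²)]/u. At p = 0.28: a = 0.583, λ = 1.202, u = 0.255, and (0.1369/0.8631)/0.255 = 0.62. So ρ = √(0.62/1.62) = 0.62. At p = 0.248 the same steps give 0.63. I use 0.62 for both; the AUC is about 0.80.

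**Step 3: cut-offs.**
- Accuracy is greatest where P(OSA | x) = 0.5, that is x = a/ρ.
- Sensitivity + specificity is greatest where P(OSA | x) = p, that is x = a[1 − √(1 − ρ²)]/ρ.
- In both cases sensitivity = P(X > x, Y > a)/p.

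For p = 0.28 and ρ = 0.37, the accuracy cut-off is 0.583/0.37 = 1.575 SD above the mean and the other is 0.112 SD.

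| p | ρ | Accuracy rule: sens / spec | Correct | Max sens + spec: sens / spec | Correct |
|---|---|---|---|---|---|
| 24.8% | 0.37 | 7% / 98% | 75.6% | 64% / 62% | 62.2% |
| 28% | 0.37 | 12% / 97% | 72.8% | 64% / 62% | 62.1% |
| 24.8% | 0.62 | 35% / 94% | 79.2% | 74% / 70% | 71.4% |
| 28% | 0.62 | 40% / 92% | 77.3% | 74% / 70% | 71.4% |

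Calling every driver negative would score 75.2% and 72.0%.

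**Step 4: where the result stops holding.** In an equal-variance binormal model with separation d, AUC = Φ(d/√2) and the accuracy cut-off, measured from the non-OSA mean, is c = d/2 + ln[(1 − p)/p]/d.
- Sensitivity is 50% when c = d, so d = √(2 ln[(1 − p)/p]). At p = 0.28, d = 1.37 and AUC = 0.83; at p = 0.248, d = 1.49 and AUC = 0.85.
- At p = 0.5 the log term vanishes and both rules give c = d/2.
- At AUC 0.70 the accuracy rule gives sensitivity / specificity of 13% / 97% at p = 0.25, 65% / 65% at p = 0.50 and 82% / 43% at p = 0.60. The test is the same; only the sample mix differs.

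**Step 5: samples of 82.** Simulating the empirical rule in the bivariate model (4,000 replicates per setting) gave a mean apparent sensitivity of 19% and 23% (p = 24.8% and 28%) with ρ = 0.37. With the range-corrected ρ (0.63 and 0.62) it was 42% and 45%. Apparent sensitivity was below 50% in 93% and 90% of samples in the first case, and in 63% and 56% in the second.

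**The case against.** Several points on the other side have force.

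- **How errors are counted.** A reader might infer that the rule counts a missed case as a third of a false alarm. It does not: each is one misclassified person. The factor of 0.33–0.39 applies to a point of sensitivity against a point of specificity, because there are fewer cases than non-cases.
- **The low figures.** A reader might infer that the rule amounts to calling nearly everyone negative. That fits only the pessimistic end, where r = 0.37 is carried over to all drivers. The correlation was reported within OSA patients, a restricted range, so the all-driver value may well be higher.
- **Prevalence.** A reader might infer that the plan will miss most drivers with OSA. The cited figures come from truck drivers and city men, and the article does not show how those studies defined OSA. Prevalence at AHI ≥ 5 in these bus drivers is unknown and is itself a secondary objective. At AUC 0.80, sensitivity under the accuracy rule reaches 50% at p of about 0.33.
- **Cost of errors.** The protocol never ranks missed cases above false alarms, and the Discussion notes that diagnostic procedures are costly. A prevalence-dependent cut-off can also be defended for one fixed target population.
- **Reach.** The main objective and the sample size rest on the association with AHI. All participants are to have polysomnography whatever the NEP result, and referral follows that diagnosis. The ROC curve is unaffected, so a reader of the results could pick another operating point.

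These points lower the severity and make the size conditional. They do not remove the mismatch. The article fixes one rule, states a screening purpose, stresses the harm of under-diagnosis in the Background, and cites only prevalences below one half for men. A volunteer sample is also a weak basis for a prevalence-tuned threshold.

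**Conclusion.** The concern holds in a conditional form. The accuracy rule ties the NEP cut-off to the OSA share of the sample. At 24.8–28% prevalence, expected sensitivity is about 7–12% with ρ = 0.37 and about 35–41% with ρ near 0.62, against about 64–74% when sensitivity + specificity is maximised. These figures assume bivariate normality and prevalences borrowed from other populations.

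The flat statement that most cases will be missed is not supported. It fails at an AUC above about 0.83–0.85 and as prevalence nears 50%, and above 50% the loss falls on specificity. The documents settle neither AUC nor prevalence for these drivers. Nor do they support calling this a fatal flaw, since neither the sample size nor participants' care depends on the cut-off. It should be fixed as a cheap improvement.

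**What to change.** Replace the cut-off criterion with one that does not depend on sample prevalence, and fix it before the data are seen. There are two options:

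- the cut-off with the highest specificity at a minimum sensitivity set in advance by the investigators, which best fits screening; or
- the cut-off that maximises sensitivity + specificity (Youden index). This is simpler, but in the models above it still leaves about a quarter to a third of cases undetected (26–36%).

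Report the AUC, and sensitivity and specificity at the chosen cut-off, each with a 95% confidence interval.

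The change is one sentence and needs no new data. Its price is a lower headline percentage correctly classified: under the Youden rule about 62–71%, instead of about 73–79%. With a sensitivity floor, the figure depends on where the floor is set.
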